### **11.5.1. Data Sets**

The primary statistical analysis will use the modified intent-to-treat patient population using observed data. The primary timepoint of interest is the day of carotid endarterectomy surgery.

## **11.6. General Considerations for Data Analysis**

### **11.6.1. Withdrawal**

If a subject withdraws prior to carotid endarterectomy surgery they cannot be included in the primary analysis as they will have no plaque data available.

### **11.6.2. Missing Data**

In this study plaque Lp-PLA2 activity data will only be obtained at the end of treatment. The behaviour of this data and plaque biomarker data after two weeks of SB 480848 treatment is not known. Neither is the relationship to plasma data known. Therefore no imputation of plaque data will be performed.

In this study plasma samples will be taken during treatment, Visit 3. However this visit is before drug plasma levels are modelled to have achieved steady state. Therefore to keep plaque and plasma data on as consistent a basis as possible no imputation or carrying forward of plasma data will be performed.

If no Visit 2 (randomisation), value is available for an efficacy assessment variable then the baseline value will remain missing and the subject cannot be used in any summary of change from baseline for this variable. For laboratory safety assessments if no Visit 2, randomisation visit, value is available but a Visit 1, screening visit, value is available then this will be used as baseline.

### **11.6.4. Assessment Windows**

All data will be reported according to the nominal time point for which it was recorded.

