### **6. STUDY ASSESSMENTS AND PROCEDURES**

A Time and Events Table is shown in Appendix 1.

Screening procedures should be conducted over a maximum period of 4 weeks prior to Visit 2 (baseline/randomisation).

The visit window for weekly visits is +/- 2 days. Study medication should be taken for 14(+/- 4) days. Visit 5 (day of surgery) must be conducted on the day following the last dose of study medication. Visit 6 must be conducted on the day after surgery, ie. 2 days following the last dose of study medication.

Visit 7 (follow-up) should be conducted 14 days (+/- 3 days) following the last dose of study medication.

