### 9.2. Patient Withdrawal

#### 9.2.1. Patient Withdrawal from Study

Each patient participating in the study will be assigned a unique CRF/patient number. Enrolment to the study will continue until 99 patients have been randomised into the study. Study medication given to withdrawn patients will **not** be reused.

Patients who terminate their participation in the study due to adverse experiences should be followed up as appropriate (see Section 10) in order to determine the final outcome.

Every effort should be made to follow up patients who withdraw or are withdrawn from the study prematurely. CRFs of **all** patients entered into the study must be completed. For patients who withdraw prior to randomisation (i.e. during the run-in period), complete the Study Continuation/Withdrawal page in the CRF.

For patients withdrawing after randomisation complete the Study Conclusion page and the Early Withdrawal (7) Visit. Reasons for withdrawal must be noted on the Study Conclusion page for all randomised patients who do not complete the study. At the patient's final visit, collect any unused study medication, and record the date of the last dose of study medication on the Study Conclusion page.

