### 11.5. Analysis Populations

The populations to be evaluated are:

- modified intent-to-treat: patients receiving at least one-dose of study medication and having valid Lp-PLA2 activity data from carotid plaque.
- intent-to-treat: patients receiving at least one-dose of study medication and having at least one efficacy assessment post-randomisation
- evaluable: subset of modified intent-to-treat population of patients who have at least 10 days of study medication, are between 80 and 120% compliant with medication, as defined in Section 11.6.3, and have carotid endarterectomy surgery within 24 hours of last dose of study medication.
- safety: patients receiving at least one dose of study medication.

For efficacy, the modified intent-to-treat population is of primary interest. The primary analysis will be repeated in the evaluable patient population as a sensitivity check. If the analyses are consistent then all plaque efficacy analyses will be performed on the modified intent-to-treat population only. If the analyses are inconsistent then data from non-evaluable patients will be reviewed in detail to identify the reason for the discrepancy, if possible. Unless a reason for discrepancy is apparent other analyses will be repeated in both populations. For plasma efficacy analyses the dropout rate and possible relation of the dropout pattern to treatment group will be assessed. If appropriate, plasma efficacy analyses may be repeated for the intent-to-treat population.

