### **11.8.3. Clinical Laboratory Evaluations**

The readings obtained at Visit 2 (randomisation) of each laboratory test will be used as the baseline value for that test. Laboratory data will be summarised for each parameter at all visits by treatment group. Absolute change from baseline will also be calculated for each subject and summarised by visit and treatment group.

A laboratory value that is on or within the reference range is considered normal. A laboratory value that is outside the testing laboratory's reference range is considered an abnormal laboratory value. A laboratory value that is above the upper limit of the reference range is considered high abnormal. A laboratory value that is below the lower limit of the reference range is considered low abnormal.

The threshold laboratory values are defined in terms of a multiplicative factor of the testing laboratory's reference range or as an absolute value. A threshold value may also be defined as a change of clinical concern from baseline. These will be defined in the Reporting and Analysis Plan (RAP). A laboratory value that is above the threshold is considered a high threshold value. A laboratory value that is below the threshold is considered a low threshold value. The proportion of patients exceeding the threshold criteria for each of these laboratory values at any post-baseline visit will be summarised by treatment group. A subject's post-baseline laboratory value will only be considered to be a threshold if it is more extreme than the baseline result and satisfies the criteria for a threshold value as defined above. A listing of patients with any threshold value during the study will also be produced.

Box plots will be used to display graphically all safety laboratory values. Any outliers will be detailed in a supporting listing.

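### The early-withdrawal visit shares number 7 with the post-surgery follow-up, and reporting by nominal time point leaves no way to keep the two apart

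*Protocol*

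**What the plan says.** All references are to the protocol.

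- **Scheduled Visit 7.** Section 6: "Visit 7 (follow-up) should be conducted 14 days (+/- 3 days) following the last dose of study medication". Appendix 1 gives the same timing. Surgery is the day after the last dose, so a patient on schedule is then about 13 days post-operative.
- **Early-withdrawal visit.** Section 9.2.1: "For patients withdrawing after randomisation complete the Study Conclusion page and the Early Withdrawal (7) Visit". No day is given. The section adds "At the patient's final visit, collect any unused study medication" and has the date of the last dose recorded on the Study Conclusion page.
- **Reporting rule.** Section 11.6.4: "All data will be reported according to the nominal time point for which it was recorded". That sentence is the whole section.
- **Safety summaries.** Section 11.8.3 summarises laboratory data at every visit and continues: "Absolute change from baseline will also be calculated for each subject and summarised by visit and treatment group". Section 11.8.4.1 does the same for vital signs.
- **Efficacy populations.** Section 11.6.1: "If a subject withdraws prior to carotid endarterectomy surgery they cannot be included in the primary analysis". Section 11.5 limits the modified intent-to-treat population to "patients receiving at least one-dose of study medication and having valid Lp-PLA 2 activity data from carotid plaque", and says of the wider population: "If appropriate, plasma efficacy analyses may be repeated for the intent-to-treat population". Section 11.7.2 ties that repeat to more dropout than expected.

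**The concern.** One visit number covers two different clinical situations. A scheduled Visit 7 is off drug and post-operative. An early-withdrawal visit may come from a patient who has not had surgery and who may have taken a dose recently. The only stated reporting rule follows the visit label, so both kinds of record fall in the same column.

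Visit 7 is the only scheduled assessment well after the end of dosing. By-visit changes in laboratory values, vital signs, plasma Lp-PLA2 and biomarkers at Visit 7 will naturally be read as the state of patients two weeks after drug and surgery. Mixed records blur that reading. Any carry-over from recent dosing would appear only on active treatment, and more at 80 mg than at 40 mg.

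**Working it through.** The plan gives no figure on this point. Its sample size (27 per group for 90% power) reproduces, at 90.5% by the noncentral t, but does not bear on the question. The check is a comparison of the passages, followed by an illustration of size.

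**Step 1. The two visits side by side**

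| | Scheduled Visit 7 | Early Withdrawal (7) |
|---|---|---|
| Time since last dose | 14 (+/-3) days | not stated in 9.2.1 |
| Surgery | about 14 - 1 = 13 days earlier | may not have happened |
| Reported as (11.6.4) | nominal time point | nominal time point |

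There are two readings of the missing timing. If the visit is held promptly, both drug exposure and surgery status differ from a scheduled Visit 7. If Section 6 is applied literally, the patient is off drug, but one who withdrew before surgery may still be unoperated. The two kinds of record are not comparable on either reading.

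**Step 2. How much drug exposure could differ**

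Input: half-life 25-45 h (Sections 1.1 and 1.3). Fraction of drug remaining = 0.5^(hours / half-life).

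| Time since last dose | 25 h half-life | 45 h half-life |
|---|---|---|
| 1 day (24 h) | 51% | 69% |
| 2 days (48 h) | 26% | 48% |
| 11 days (264 h, early edge of window) | 0.07% | 1.7% |
| 14 days (336 h) | 0.01% | 0.6% |

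**Step 3. Shift in a nominal Visit 7 mean for plasma inhibition**

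Inputs: expected steady-state trough inhibition of 60-65% at 40 mg and 85-90% at 80 mg (Section 7.3), and 33 patients per group (Section 11.4.1). Assumptions: the withdrawal visit is within about a day of the last dose, inhibition is at the full trough level, scheduled Visit 7 inhibition is near zero, and all 33 patients contribute a Visit 7 value.

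Shift = (k / 33) x inhibition, where k is the number of such patients.

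| k of 33 | 40 mg (points) | 80 mg (points) |
|---|---|---|
| 1 | 1.8-2.0 | 2.6-2.7 |
| 3 | 5.5-5.9 | 7.7-8.2 |
| 6 | 10.9-11.8 | 15.5-16.4 |

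Placebo shifts by zero. Six is close to the whole dropout allowance (20% of 33 = 6.6). That allowance also covers unevaluable plaque, so six is near an upper bound.

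**Step 4. Which analyses can be reached**

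- *Primary plaque analysis:* none. Patients without plaque are excluded, and plaque has no Visit 7 value.
- *Modified intent-to-treat plasma analyses:* only patients who withdraw after surgery. They are operated and past their last dose, but a prompt visit would precede the 14-day point.
- *Conditional intent-to-treat repeat of the plasma model:* pre-surgery withdrawals enter. Time is first fitted as linear, so the label matters. If planned days were used, a day-7 withdrawal coded as Visit 7 would sit near day 14 + 14 = 28, three weeks late.
- *By-visit laboratory and vital-sign summaries:* withdrawals who received drug are in the safety population and enter.
- *Peripheral lymphocytes:* Section 6.2.4.2 and Appendix 1 sample at Visits 2 and 7 only, so a withdrawal sample is that patient's sole post-baseline value. (Section 1.1 names Visits 2 and 5, a separate inconsistency.)
- *Laboratory threshold summary (11.8.3):* counts any post-baseline visit, so the label does not matter.

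**The case against.** The strongest reply has four parts.

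1. **No passage says that withdrawn patients are seen at once.** A reader might infer this from the visit's name and from the collection of unused tablets at the final visit, but neither fixes a day. The only timing rule for a Visit 7 is anchored to the last dose and could apply to someone who stops early. This stands: on-drug sampling is a possibility, not a stated fact.
2. **No passage says that the two kinds of record are pooled.** The visit has its own name and could be treated as its own nominal time point. This stands in part. The name also carries the number 7, and 11.6.4 contains nothing that tells the two apart.
3. **Visit slotting belongs in the Reporting and Analysis Plan**, which is not at hand and may already deal with it. That would be decisive if the protocol were silent. It is not: 11.6.4 sets a rule without exception, and 11.6.5 treats departures from protocol analyses as deviations to be described.
4. **The consequences are narrow.** Pre-surgery withdrawals reach plasma results only through a conditional repeat. Adverse events leading to withdrawal are tabulated separately, vital signs are listed in full, and no listed objective concerns recovery after drug. This stands and limits the importance of the point.

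**Conclusion.** The point holds as a defect of labelling and reporting, of modest weight. The protocol gives one number to two different visits, leaves the timing of one unstated, and reports by nominal time point. By-visit laboratory and vital-sign summaries, the Visit 7 lymphocyte result and any intent-to-treat repeat of the plasma model can therefore mix unoperated, possibly recently dosed patients with true follow-up. This does not depend on how the timing is read, because surgery status can differ either way.

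The size does depend on timing. With prompt visits, full trough inhibition and 33 values per arm, each affected patient moves mean Visit 7 inhibition by at most about 2.7 points at 80 mg and 2.0 at 40 mg. Patients who stop before steady state, reached at about 10 days, may contribute less.

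A reader might go further and infer a false residual dose response of 4 to 16 points, or a bias in the trial's main result. The documents support neither. The first needs two to six promptly sampled withdrawals per arm in a repeat that may never be run. The second is ruled out by Sections 11.5 and 11.6.1.

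**What to change.** Amend Section 11.6.4 as follows:

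- Report early-withdrawal assessments as a separate time point, not as Visit 7.
- Admit to the Visit 7 summaries only samples taken 14 (+/-3) days after the last dose and after surgery.
- In any plasma repeated-measures model, place early-withdrawal records by actual time.

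Sections 6 and 9.2.1 should also be reconciled so that the intended timing of the withdrawal visit is explicit. What that timing should be is for the sponsor to state.

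The cost is a short amendment to 11.6.4 and a matching slotting rule in the Reporting and Analysis Plan. The last-dose date is already collected. The downside is slightly fewer records in the Visit 7 column.

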### **11.6.5. Other Issues**

Any deviations from the analyses described in the protocol will be described in the Reporting and Analysis Plan (RAP) and final Study Report as appropriate.

No separate analyses of subgroups will be performed, though summaries by risk factors will be produced. The effects of risk factors will be assessed by including them in an analysis of covariance.

### **11.7.2. Secondary Analysis**

Plasma Lp-PLA2 levels will be analysed as longitudinal data, using mixed effects for repeat measures, and testing for treatment effect. The analysis will be performed using the multiple record per patient form for the data so patients with partial data are included in the analysis. Fixed effects to be included in the model are the stratification variables of statin use and gender, the known risk factor of age, and treatment, in the order given. Subject will be a random effect.

Initially time will be modelled as a linear effect. This will be assessed by plotting overlaid individual subject graphs. If linearity is not appropriate interaction of time and treatment will be investigated: a 10% significance level will be used to declare effects as formally significant.

If there is a higher than anticipated level of dropouts the analysis will be repeated in the intent-to-treat population to assess whether there is any differential effect due to treatment related dropout. Results of modelling of Watanabe rabbit plasma LpPLA2 levels will be reviewed prior to unblinding of this study and the proposed analysis modified if appropriate.

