If it is not logistically possible to take the PK/PD (Lp-PLA2) samples during Visit 4 (0.5 - 2, 2.5 - 4; and 6 - 12 hours post dose) because the patient is unable to arrive early in the Hospital, then these samples can be taken at Visit 3.

The final PK blood samples will be taken at any time on the day after surgery

Lp-PLA2 Blood sampling: A single blood sample will be collected at V2, V5, V6 and V7. At Visit 4 (or V3 if it is not logistically possible to take these samples at V4) blood samples will be collected as described in Table 1 (Pre-dose, 0.5 –2hr, 2.5 –4hr and 6 - 12hr).

Every effort should be made to collect samples at times spread throughout the time window (i.e., avoid collections from all patients at the same time within a window or only at the extremes of a time window).

In addition to PK/PD samples, another blood sample will be taken at each timepoint. At the end of the study, if appropriate, these samples may be used to measure levels of some of the defined biomarker(s) (Section 6.4) which have demonstrated a change throughout the course of the study.

Samples will be prepared and shipped to Quest Diagnostics. Full details will be provided separately. Quest Diagnostics will store and ship the samples to GSK, where they will be analysed using approved assay techniques.

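### Plasma Lp-PLA2 mixed model (Protocol 11.7.2): subject is the only random effect named although four of eight samples fall on one day, so the 10% time-by-treatment test can run above its level

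*Protocol*

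**What the plan says.** Protocol 11.7.2 analyses plasma Lp-PLA2 levels "using mixed effects for repeat measures, and testing for treatment effect". The fixed effects are statin use, gender, age and treatment. The random part is given in one sentence: "Subject will be a random effect". No visit or day effect, random slope or residual correlation is named. On the records, it says: "The analysis will be performed using the multiple record per patient form for the data so patients with partial data are included in the analysis".

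On time, it says: "Initially time will be modelled as a linear effect". If linearity does not fit, "interaction of time and treatment will be investigated", with a 10% significance level. How time is then coded is not stated.

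The plasma Lp-PLA2 schedule is in 6.3.2 and 6.5.1. "A single blood sample will be collected at V2, V5, V6 and V7"; at V4, or at V3 where V4 is not practicable, "blood samples will be collected as described in Table 1 (Pre-dose, 0.5 –2hr, 2.5 –4hr and 6 - 12hr". That makes eight records per patient, four of them on one day. Section 6.3.2.1 lists these post-dose samples under plasma Lp-PLA2 activity, so their entry into the 11.7.2 model is a natural reading, though it is not spelled out.

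**The concern.** A random intercept for subject makes any two samples from one patient equally correlated, whether taken two hours or two weeks apart. Samples from the same day may also share that day's deviation: physiology, handling, assay run and, on drug, exposure. If they do, the four same-day records carry less information about change over time than the model credits. The residual mean square is then too small, and within-patient contrasts get standard errors that are too small.

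The test at risk is time by treatment. V2 is pre-dose, so within this model a drug effect that develops after baseline shows up as a time-by-treatment interaction. Change in blood Lp-PLA2 activity and mass are secondary objectives (Protocol 2.2).

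**Working it through.** **Inputs.** From the protocol: 27 modified intent-to-treat patients in each of 3 groups (11.4.1); 8 records (6.5.1); nominal days 0, 14 (four samples), 15, 16 and 28, or with the four samples on day 7 (Appendix 1 and section 6); test level 10% (11.7.2). Assumed: a share q of within-patient variance is common to samples from the same day. The protocol gives no value, so q is varied from 0 to 0.9.

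**Step 1: what the model takes as residual variance.** Set the within-patient variance to 1. The squared numbers of samples per day sum to 1 + 16 + 1 + 1 + 1 = 20. The expected within-patient sum of squares is q(8 − 20/8) + 7(1 − q) = 7 − 1.5q. On 7 degrees of freedom the residual mean square is 1 − 0.214q, too small whenever q > 0.

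**Step 2: true variance of the slope, linear time.** With x the centred day, A = Σx² and B = Σ(day total of x)², the true slope variance relative to 1/A is (1 − q) + qB/A.

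- Sampling at V4: mean day 14.375, A = 395.9, B = 397.6, B/A = 1.004.
- Sampling at V3: mean day 10.875, A = 514.9, B = 695.1, B/A = 1.350.

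**Step 3: size.** The ratio of true to model variance is r = [(1 − q) + qB/A] / (1 − 0.214q). Comparing three slopes is a 2-df test, for which the large-sample size is 0.10^(1/r).

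Example, V4 sampling, q = 0.5: r = 1.002/0.893 = 1.122 and 0.10^(1/1.122) = 12.8%.

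| q | r, V4 | size, V4 | r, V3 | size, V3 |
|---|---|---|---|---|
| 0 | 1.000 | 10.0% | 1.000 | 10.0% |
| 0.25 | 1.058 | 11.3% | 1.149 | 13.5% |
| 0.5 | 1.122 | 12.8% | 1.316 | 17.4% |
| 0.75 | 1.195 | 14.6% | 1.504 | 21.6% |
| 0.9 | 1.244 | 15.7% | 1.629 | 24.3% |

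The row q = 0 reproduces the stated 10%. At q = 1, V4 sampling reaches 16.5%.

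**Step 4: simulation and other time codings.** Random-intercept F tests under no drug effect, 3 × 27 patients, 10,000 trials per setting, nominal 10%:

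| q | linear, V4 | linear, V3 | eight nominal times | five-level visit |
|---|---|---|---|---|
| 0 | 10.1% | 10.4% | 10.4% | 10.3% |
| 0.25 | 11.3% | 13.2% | 10.6% | 17.3% |
| 0.5 | 13.2% | 17.3% | 11.9% | 26.6% |
| 0.75 | 14.3% | 22.1% | 13.5% | 37.1% |
| 0.9 | 15.7% | 25.5% | 14.9% | 42.0% |

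Separate runs differ from these by about a point, hence the rounded ranges 11–16%, 13–25% and 17–43%. A REML fit with linear time, V4 sampling and 10% of records missing (500 trials) gave 9.2%, 12.8% and 18.6% at q = 0, 0.5 and 0.9.

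**Step 5: why coding matters.** With a five-level visit factor, the four same-day samples are replicates of one level. The mean square for the four between-day contrasts averages (4 + 1.5q)/4 = 1 + 0.375q, while the error term averages 1 − 0.214q. At q = 0.9 that is 1.338/0.807 = 1.66. With eight separate times, numerator and denominator have the same average, and only the unequal variances of the contrasts inflate the test.

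**Step 6: treatment main effect.** This compares patient means. Over q = 0 to 0.9 it ran at 9.7–10.5% at nominal 10% and at 4.6–5.3% at nominal 5%, so it keeps its level.

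**The case against.** **The text does not say subject is the sole correlation term.** It excludes no residual covariance, and the Reporting and Analysis Plan may specify one. Section 11.10.2 also directs PD data to the PK/PD analysis. This stands in part: entry of all four samples is an inference, so the point is conditional on it. But 11.7.2 does name a random part, and followed as written it is a random intercept. Section 11.10.2 rules out only a separate population PD analysis.

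**The affected test is a conditional follow-up.** The named test is the treatment effect, which keeps its level. Section 11.7.3 repeats the primary method on change from baseline in plasma Lp-PLA2, so the secondary objective has an analysis that does not depend on the random intercept. Both stand, and they limit the harm.

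**Stronger readings a reader might infer.** One is that the four samples count as four independent visits. They do not: they share the subject effect and are independent only given the patient. Another is that the test rejects far more often than stated. That holds only for a five-level visit factor or, less strongly, V3 sampling, with a substantial day effect. The protocol states neither that coding nor the size of the effect. Section 11.6.4 reports by nominal time point, and Table 1 gives the four samples separate times, which points at least as much to eight times. A third is that the plasma biomarkers sent to this model by 11.9 are affected. Scheduled biomarkers are drawn once per visit (6.4), so this mechanism does not reach them.

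**Conclusion.** The point holds in a limited form. As written, the model has no term for same-day correlation, while half of each patient's scheduled records come from one day. If all eight enter and a day effect exists, the 10% time-by-treatment test is anti-conservative: by about 1 to 6 percentage points with linear time and V4 sampling or with eight nominal times, 3 to 15 points with linear time and V3 sampling, and 7 to 33 points with visit as a five-level factor.

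These figures rest on an assumed day share of 0.25 to 0.9, equal variance on each day, and all patients on the same sampling option. With no day effect there is no excess. The treatment main effect, the primary plaque analysis and the change-from-baseline analysis in 11.7.3 are not affected. This is a worthwhile, inexpensive improvement to a secondary analysis, not a threat to the trial's main conclusion.

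**What to change.** In 11.7.2, state which of the V4/V3 samples enter the model, and choose one of two routes:

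- Keep all eight records and add a random subject-by-visit (day) effect beside the subject effect. The four same-day samples allow its variance to be estimated. In a REML check with V4 or V3 linear time or a five-level visit (700 trials each, q = 0.25 and 0.9), the nominal 10% test ran at 9–12%, within simulation error of its level.
- Enter one prespecified value per visit, for example the pre-dose sample, with visit as a category. With the pre-dose value, size was 9.4–10.1%. With the mean of the four samples it was 9.6–10.5% for q = 0.25 to 0.9.

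Under either route, record whether the sampling day was V3 or V4 and use the actual day, so that a day-7 set is not analysed as day 14. An unstructured covariance across visits does not by itself settle this: the set is taken at V3 instead of V4, so the data carry little or no information on the covariance between those two visits.

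The cost is wording in 11.7.2 and the Reporting and Analysis Plan. No new samples are needed. Intervals become slightly wider, and the first route adds one variance parameter.
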